#### DNA Methylation

Epigenome-wide DNA methylation will be evaluated using DNA extracted from frozen whole blood samples. Genomic DNA will be bisulfite converted and hybridized to Illumina Infinium MethylationEPIC BeadChip arrays at the lead site. Changes in DNA methylation (differentially methylated positions) will be expressed as population medians. Medians will be used to identify changes between responders and nonresponders that meet both the significance cutoff of *P*<.05, and a threshold of >10% change.

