### Statistical Methods

#### Sample Size Calculation

This is a longitudinal study of 150 patients with MS entering the study and predicted to have no more than 20% dropout. Over the study period, we expected 120 patients with MS with longitudinal data for all measured factors: clinical, cellular, and omics. On the basis of CLARITY and CLARITY extension study data, we expect approximately 50% of patients with MS (n=60) to exhibit disease activity according to NEDA 3 (ie, nonresponders) [7-10].

We performed a detailed simulation analysis to assess the power of our sample sizes to detect significant associations at a range of effect sizes and for a range of significance thresholds as per the recommendations of Tsai and Bell [45]. With 120 cases (60 responders vs 60 nonresponders), this study will have 80% power to detect a minimum mean biomarker difference of 10% at a Benjamini-Hochberg false discovery rate of 0.05, which will reasonably balance type I and type II errors. To detect more minor differences, we will use a penalized regression analysis within a machine learning framework using the GLMNet tool [46]. This method is designed for studies with large numbers of predictors and will further enhance the power to identify multi-marker signatures that are predictive of patient response (see details below in the *Association Modeling* section).

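### For methylation positions declared under the article's two-part rule, the stated 80% power at a 10% difference falls to about 50% if both 10% figures share a scale

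*Protocol article*

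**What the plan says.** In the protocol article, Methods, DNA Methylation, group medians are used to find changes between responders and nonresponders. A change must satisfy two conditions together: P<.05, "and a threshold of >10% change".

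In the Sample Size Calculation, the planned intake is "150 patients with MS entering the study and predicted to have no more than 20% dropout", which leaves "120 patients with MS with longitudinal data for all measured factors: clinical, cellular, and omics". For the comparison of 60 responders with 60 nonresponders, the article claims "80% power to detect a minimum mean biomarker difference of 10% at a Benjamini-Hochberg false discovery rate of 0.05".

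The power sentence names a significance criterion and nothing else. Neither section says whether its 10% is in absolute methylation points or relative to the level in one group.

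**The concern.** The same number, 10%, is both the true effect at which power is claimed and the size that the observed effect must exceed. A filter placed at the assumed true effect removes about half of the estimates, however precise they are. The power sentence covers omics, and methylation is the only omics measure whose analysis is set out (RNA is stored for later). A reader will therefore take the 80% to apply to the methylation rule.

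At stake is how that arm is read. An empty list of declared positions would look like stronger evidence against 10% differences than it is, and positions that pass near the threshold would tend to overstate their effect.

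**Working it through.** **Inputs.** From the Sample Size Calculation: 150 enrolled, 20% dropout, 60 v 60, 80% power, difference 10%, Benjamini-Hochberg FDR 0.05. From DNA Methylation: P<.05 and an observed change above 10%, on medians. Not given, so assumed: the per-test alpha implied by the FDR (range 0.05 to 6e-8, two-sided), the SD, and the scale of each 10%.

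**Step 1: the plan's own figures.** 150 × (1 − 0.20) = 120, which agrees. The 80% can be neither reproduced nor refuted without an SD and a per-test alpha, so I took it as true for the significance test.

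**Step 2: the bound.** P(significant and observed >10%) ≤ P(observed >10%). For an estimate centred on 10% with a symmetric distribution, the right-hand side is 0.5. No SD or alpha is needed, and a larger sample does not change it while the true difference equals the threshold.

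**Step 3: which condition binds.** Choose SE so that the test alone has 80% power at 10 points: SE = 10 / (z(1−α/2) + 0.842). The smallest significant difference is z(1−α/2) × SE. Joint power is 1 − Φ((max(critical, 10) − 10) / SE). The true difference needed for 80% joint power is max(critical, 10) + 0.842 × SE.

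| Per-test α (assumed) | SE | Critical difference | Joint power at true 10 | True difference for 80% |
|---|---|---|---|---|
| 0.05 | 3.57 | 7.0 | 50% | 13.0 |
| 0.001 | 2.42 | 8.0 | 50% | 12.0 |
| 1e-5 | 1.90 | 8.4 | 50% | 11.6 |
| 1e-6 | 1.74 | 8.5 | 50% | 11.5 |
| 6e-8 | 1.60 | 8.7 | 50% | 11.3 |

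Worked line, α = 0.05: SE = 10 / (1.960 + 0.842) = 3.57; critical = 1.960 × 3.57 = 7.0; needed = 10 + 0.842 × 3.57 = 13.0. The critical difference is below 10 in every row, so the filter is what binds.

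**Step 4: simulation (20,000 runs, 60 v 60, t-test for significance).** Normal data, true difference 10 points, α of 0.05, 1e-4 and 1e-6: joint power 50-51% with the filter on means and 47-49% with it on medians. Beta-distributed data with a mean difference of 10 points, α = 0.05: about 50% on means and 54-59% on medians. The median figure is higher because the true median difference is then 10.3-10.7 points. In these beta runs the test alone had 95-100% power, so they isolate the filter.

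**Step 5: mixed scales (α = 0.05, mean methylation levels 0.2, 0.5 and 0.8).**
- Relative filter, absolute 10-point power difference: the filter sits at 2, 5 and 8 points and the critical difference is 7.0. Joint power is 80%, 80% and 71%; the last is 1 − Φ((8 − 10) / 3.57).
- Absolute 10-point filter, relative power difference: the true differences are 2, 5 and 8 points. Joint power is about 0%, 0.3% and 24%.

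**The case against.** The strongest reply is that the power sentence belongs to another analysis. It speaks of biomarkers generally and of an FDR. That matches Association Modeling, where each biomarker is modelled individually and Benjamini-Hochberg adjusted with no 10% filter. This stands: nothing here shows that 80% is wrong for those models or for other biomarkers. It does not remove the point, because the Sample Size Calculation includes omics and does not exempt the methylation rule.

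A reader might infer that power cannot exceed 50% whatever the circumstances. The article does not support that. It gives no scale for either 10%, and it states power for means while the rule uses medians; steps 4 and 5 show what both do to the figure. The filter could also be read as applying to change over time, since change from baseline in methylation is a listed outcome. The methylation sentence does tie it to the responder/nonresponder contrast, so a common scale is the natural reading, but it remains an assumption.

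A reader might also infer that filtered positions are lost to the study. They are not: the individual models carry no such filter, and the elastic net runs on the whole factor set and is intended for smaller differences.

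Finally, a minimum-effect filter is a legitimate design choice. That is granted; the defect is that the stated power does not describe the filtered rule. Nor is this a detail that can be left to the analysis plan, because both statements are in the article and conflict on the natural reading.

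**Conclusion.** The point holds in conditional form. For methylation positions declared under the two-part rule, the 80% does not apply at a true 10% difference if both 10% figures are on one scale and the mean and median differences are about equal; power is then about 50%. Skewed data raise it to about 54-59%, still well short of 80%. Only a relative filter combined with an absolute power difference would bring it near the claim (71-80%); the reverse mix makes it far worse (0-24%).

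The reach is limited. Methylation is an additional outcome, the primary outcome is NEDA 3 response, and the enrolment arithmetic is sound. The use of P<.05 in the methylation rule against an FDR elsewhere is a separate question; the same-scale result holds under either.

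**What to change.** 1. State for each 10% whether it is absolute methylation points or relative change.
2. Restate the power sentence so that the 80% refers to the FDR test alone. Add that, with both figures on one scale, power under the methylation filter is about 50% at a true 10% difference and reaches 80% only at about 11.5-13% (means, normal data, assumed per-test alpha 1e-6 to 0.05; about 11.3% at 6e-8).
3. Rerun the existing simulation with the complete methylation rule, applied to medians, and replace these approximate figures with its results.

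Keeping >10% only as a descriptive flag beside an estimate and confidence interval is an option, not a required correction; it would lengthen the list of declared positions.

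The cost is a sentence or two and a rerun of a simulation the article says was done. Recruitment is complete, so the sample size is not in play. The downside is a less favourable stated detectable difference for methylation.

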#### RNA or Gene Expression Analysis

RNA will be collected in PaxGene tubes and stored for future analysis, as per funding.

#### End Points and Outcomes

Participants will attend visits or receive phone calls for assessments at baseline (before 1st dose) and months 1 (before 2nd dose), 3, 7, 12 (before 3rd dose), 13 (before 4th dose), 18, 24, 30, 36, 42, 48, 54, 60, 66, and 72 months, and a variable time point (Tv; at exacerbation of disease and/or before change in treatment or redosing). The schedule of the assessments is shown in Multimedia Appendix 1. BICAMS will be performed annually. MRI will be performed yearly, plus one additional scan 6 months after the first treatment course. Lymphocyte subsets (TBNK and B memory panels) will be performed at screening and at 3, 7, 12, 18, 24, 36, 48, 60, 72, and Tv. Serum NfL will be assessed at screening and at 3, 7, 12, 18, 24, 36, 72, and Tv. DNA methylation and RNA collection occur at screening and at 7, 24, 72, and Tv.

### End Points

The primary end point for all outcome measures is the proportion of patients with MS achieving NEDA status (responders) at 6-years relative to screening. However, preliminary end points will also be considered at each of the major biomarker collection points (months 7, 24, 48, and Tv).

The key outcome measures will be NEDA 3 or 4 responders after 6-years. Additional outcome measures will change over time from baseline in MRI parameters (brain volume loss, lesion load, and lesion volume), cognition, lymphocyte subsets, sNfL, and global DNA methylation profiles. In addition, the Tv time point will be used to determine if there are any changes in biomarker status that may predict disease activity. This will be compared with the time point at which the patient is deemed to have stable disease.

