### Objective

The primary objective of the study is to evaluate the safety and efficacy of cladribine tablets over a 6-year period according to NEDA 3. We will also evaluate clinical outcomes and cognition over a 6-year period, blood-based and MRI-based biomarkers for their ability to predict treatment response, disease activity, and the need to redose cladribine subsequent to the 2-year, 2 initial courses.

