## Methods

### Study Design

This study is a multicenter, 6-year, phase IV, low interventional trial. Enrollment of 150 patients with MS was planned across 9 specialist MS clinics in Australia. The Therapeutic Goods Australia approved a cumulative dose of cladribine (10 mg) tablets as 3.5 mg/kg body weight over 2 years administered as 1 treatment course of 1.75 mg/kg per year. After 3 years, patients with MS in consultation with their health care provider will discuss the option of redosing with cladribine tablets, if clinically indicated (by relapse or new MRI activity), switch to another DMT, or continue without change (without commencement of any DMT). For those who will be continued on cladribine, additional courses will be administered as per the previous dosing of 1.75 mg/kg per year.

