#### Association Modeling

Our primary outcome is treatment response status according to NEDA 3. We will perform parametric statistical analysis to determine whether any clinical parameters are associated with outcome—the dependent variable. Multiple repeated measurements of the same individual will be obtained. Therefore, we will apply generalized linear mixed models for binary outcomes, with random effects for time points to account for within-subject correlations and clustering. Clinical factors included in the primary analysis will be EDSS, MRI, and relapse rate measures regressed at baseline. Confounding factors (age, sex, disease duration, etc) will be included as required. By carefully defining covariate values in terms of lagged or leading indicators of study factors, longitudinal data will help us to establish the direction of causation and any lags involved. We will also use Mendelian randomization techniques to help dissect causation from the correlation of evidence for causality. In this analysis, all predictor biomarker variables will be modeled individually and yield a test-specific (unadjusted) *P* value. However, we will apply a Benjamini-Hochberg false discovery rate to adjust the raw *P* value for multiple testing while maintaining power. The secondary outcome variables will be modeled similarly using mixed models with specific parameters dependent on the type of data.

To identify multi-biomarker signatures that predict response in this patient cohort, we will also use machine learning algorithms on the patient cohort data set. Specifically, elastic-net regularized generalized linear model analyses using logistic, linear, or multinomial or Poisson models (depending on the outcome variable) will be conducted within a cross-validation routine to avoid overfitting. This will be performed on the entire factor set using the GLMNet package in the R program [46]. Briefly, GLMNet fits a generalized linear model via penalized maximum likelihood and is akin to a stepwise forward regression with the added feature of being able to perform internal cross-validation. GLMNet allows for both binary and multinomial outcomes. GLMNet allows for the rapid discovery of reduced factor panels that are likely to be associated with outcomes. This complementary approach is not susceptible to multiple testing burdens and will facilitate the identification of the best fitting multifactor signature that is predictive of treatment response [46].

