## Appendix

Multimedia Appendix 1 Study overview. Schedule of visits for study duration. The shaded area indicates when each study assessment was performed. Tv=clinical deterioration, Tv+=one month post redose (if applicable), Time point T15* month number is dependent on the year 2 dose (3 months post year 2 week 1). The Brief Cognitive Assessment for Multiple Sclerosis assessment will alternate between the standard and alternate versions. **Indicates magnetic resonance imaging scans to be used only if clinically applicable. X denotes the major analysis time point.

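### The comparison of Tv with stable disease is described as predictive, but a Tv sample triggered by activity is drawn at or after that activity and shows concurrent change

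*Protocol article*

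**What the plan says.** All references are to the protocol article.

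- **Use of Tv.** *End Points* states that "the Tv time point will be used to determine if there are any changes in biomarker status that may predict disease activity". The comparator follows: "This will be compared with the time point at which the patient is deemed to have stable disease". No pre-event window or lead time is attached.
- **Definition of Tv.** *End Points and Outcomes* describes "a variable time point (Tv; at exacerbation of disease and/or before change in treatment or redosing". The *Appendix* legend has "Tv=clinical deterioration, Tv+=one month post redose (if applicable".
- **Trigger for redosing.** *Study Design* offers redosing "if clinically indicated (by relapse or new MRI activity". It states no such condition for switching to another therapy.
- **Objective.** *Objective* lists evaluating "blood-based and MRI-based biomarkers for their ability to predict treatment response, disease activity, and the need to redose cladribine" after the two initial courses.
- **Other routes to prediction.** *Association Modeling* plans time-shifted covariates to judge which way an effect runs and with what delay: "By carefully defining covariate values in terms of lagged or leading indicators of study factors, longitudinal data will help us to establish the direction of" (the sentence is cut here). It adds: "To identify multi-biomarker signatures that predict response in this patient cohort, we will also use machine learning algorithms", run on the whole set of factors with cross-validation.

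**The concern.** To predict an event, a marker must be measured before it. The sentence in *End Points* gives the predictive role to a sample whose collection is, in most of its defined uses, prompted by the event. For serum neurofilament (sNfL) the article supplies the mechanism: *Neurofilaments are a Promising Biomarker* says it is shed on neuronal damage and tracks focal lesion activity. A raised sNfL at Tv is therefore what activity would produce, whether or not the marker had risen beforehand.

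At stake is how a positive result would be read. A clear difference between Tv and stable disease, reported under the label that *End Points* gives it, would be taken as evidence that the marker forecasts activity. Because activity is also the stated trigger for redosing, it could be taken further as forecasting the need to redose. The contrast could not support either conclusion.

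**Working it through.** **1. The plan's own figures.** From *Sample Size Calculation*: 150 × (1 − 0.20) = 120 evaluable patients, and 120 × 0.50 = 60 nonresponders against 60 responders. These reproduce. The stated 80% power is for that between-group comparison, not for Tv versus stable. It cannot be re-derived, because no standard deviation or number of tests is given, and it does not bear on this point.

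**2. Order of events for each reason for a Tv sample.**

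| Reason for Tv | Sequence implied by the article | Lead time for the triggering activity |
|---|---|---|
| Exacerbation | activity, then sample | none |
| Before redosing | relapse or new MRI activity, then decision, then sample, then redose | none |
| Before a switch of therapy | no activity condition stated | undetermined; the sample need not follow activity |

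In the first two rows the marker is read at or after the activity it is said to predict.

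**3. Illustration (all settings assumed).** Take a marker that rises only at the event: 60 patients with events, between-subject SD 0.7, within-subject SD 0.7, a rise of 0.5 at Tv, and no change beforehand. Over 4,000 simulated data sets, a paired test of Tv against stable was significant at 0.05 in 97%. A test of the pre-event sample against 60 responders was significant in 5%, its false-positive rate. So a marker with no predictive content can pass the first comparison almost every time. The 97% depends on the assumed values; the contrast between the two tests does not.

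**4. Age of the last scheduled sample.** Scheduled months from *End Points and Outcomes*:
- lymphocyte subsets: 0, 3, 7, 12, 18, 24, 36, 48, 60, 72
- sNfL: 0, 3, 7, 12, 18, 24, 36, 72
- methylation and RNA: 0, 7, 24, 72

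The maximum gap is the longest interval between scheduled samples that overlaps the period. For mean gaps I assume event times uniform over the period. If the last sample is at month s and events fall between months a and b, the mean gap is (a + b)/2 − s.

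For events in months 36 to 72:
- lymphocytes: three 12-month intervals, each with mean 6
- sNfL: (36 + 72)/2 − 36 = 18
- methylation: (36 + 72)/2 − 24 = 30

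| Marker | Maximum gap (months) | Mean gap, months 36–72 | Events with a sample in the previous 12 months |
|---|---|---|---|
| Lymphocyte subsets | 12 | 6 | 100% |
| sNfL | 36 | 18 | 12/36 = 33% |
| Methylation, RNA | 48 | 30 | none |

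Over the whole of months 0 to 72 the mean gaps are 4.8, 10.8 and 18.3 months.

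*Discussion* speaks of offering redosing from year 3, while *Study Design* says after 3 years. If the period is taken as months 24 to 72, the means are 6 for lymphocytes, (12² + 36²)/(2 × 48) = 15 for sNfL, and (24 + 72)/2 − 24 = 24 for methylation. The maxima are unchanged.

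The same schedule shows that a patient who stays stable without a treatment change has no scheduled sNfL sample between months 36 and 72, and no methylation sample between months 24 and 72. In those intervals Tv is the only source of these markers. *End Points* names month 48 as a major biomarker collection point, but neither marker is scheduled then.

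**The case against.** The strongest reply is that this is one additional analysis, introduced after the NEDA end points and the change-from-baseline outcomes, and that prediction is planned elsewhere. Samples are scheduled from screening onward, the powered comparison is responders against nonresponders, and *Association Modeling* already plans lagged covariates and a cross-validated elastic net. All of that stands. A reader might infer that the whole prediction programme rests on Tv and cannot forecast activity or the need to redose; the article does not support that.

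Three further limits also stand.

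- Tv is not always a sample at exacerbation. One taken before a switch need not follow activity, and any Tv sample precedes whatever happens later. It could inform later outcome or choice of therapy; the lack of lead time applies only to the triggering event.
- A reader might infer that Tv falls later than the stable sample, so that the contrast is confounded with time since the last course. The article does not say which comes first.
- The article describes release on damage for sNfL only. It does not show that lymphocyte subsets or methylation change as a result of a relapse. The timing argument needs no such mechanism, but reverse causation should not be asserted for every marker.

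What the reply does not remove is the sentence itself. The text on lags is general, concerns direction of causation and does not mention Tv. The specific statement on finding changes that may predict activity names Tv. Nor does the article say that Tv values stay out of the elastic net's factor set. Since NEDA failure is defined by activity, including them risks carrying the outcome into its own predictors. The detailed model can be left to an analysis plan; calling a concurrent contrast predictive is a statement that the article makes.

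**Conclusion.** The point holds for the comparison of Tv with stable disease. Where Tv is triggered by exacerbation, or precedes a redose that requires relapse or new MRI activity, its lead time for that activity is zero or negative, so the contrast identifies concurrent markers. This should be corrected. It does not invalidate the biomarker programme or the responder comparison.

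The size of any misleading difference depends on marker kinetics that the article does not give. What can be sized is how well the schedule supports a proper predictor: well for lymphocyte subsets (sample at most 12 months old), adequately for sNfL up to month 36, and poorly for sNfL after month 36 (up to 36 months old) and methylation after month 24 (up to 48 months old). The maxima follow from the schedule alone; the mean gaps rest on uniform event times.

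**What to change.** 1. For predicting activity, apply the lagged approach of *Association Modeling* explicitly. The predictor is the last scheduled sample before the event. Compare it with samples at the same scheduled month from patients still event-free then, by risk-set matching or a landmark analysis, adjusted for age and time since the last course.
2. Keep Tv values out of the predictors for the event that triggered them, including in the elastic net. This requires the reason for each Tv sample (exacerbation, before redosing, before a switch) to be identifiable in the data set.
3. Retain Tv versus stable, but describe and report it as an analysis of concurrent markers.
4. State the age of the predictor sample beside each result, and limit prediction claims in the redosing period mainly to lymphocyte subsets.

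The cost is wording and analysis on samples already planned. The price is weaker prediction for sNfL and methylation late in the study. Adding these assays at months 48 and 60, when lymphocyte subsets are already scheduled, would cut the maximum gap after month 48 to 12 months for both. It would need extra assays and suitable blood from those visits, and is not a condition of the correction.
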